### 5.4 Inclusion criteria

Potential study participants must meet all listed inclusion criteria in order to be eligible for participating in this clinical investigation. Patients will be recruited into this study if they have been diagnosed with a first-ever ischemic or hemorrhagic stroke, clinically stable phase of multiple sclerosis (MS), Parkinson's Disease (PD), a spastic para- or tetraplegia caused by any type of spinal cord lesion, mild to medium grade hereditary ataxia, acute or chronic inflammatory demyelinating polyneuropathy (e.g., GBS, CIDP) or a motoneuron disease (e.g., ALS). All patients must be in a clinically stable phase of their disease. Diagnoses will be confirmed using current criteria such as the Guideline of the German Society of Neurology (2017) (Hennerici & Kern, 2017) for stroke, the revised McDonald criteria valid at the time of diagnosis (Polman et al., 2011; Thompson et al., 2018) with MS, the UK Brain Bank criteria (Hughes et al., 1992) with idiopathic PD, Guideline of the German Society of Neurology (DGN 2012) or current NICE Guideline (*Spinal injury: assessment and initial management. Spinal*

*injury assessment: assessment and imaging for spinal injury. NICE Guideline NG41, 2016*), valid at the time of diagnosis, with spinal cord injury (SCI), the Ataxia Medical Guidelines 2016 or earlier versions, developed by Ataxia UK, London (de Silva et al., 2019) with hereditary ataxias, the diagnostic criteria originally developed by the National Institute of Neurological Disorders and Stroke (NINDS) ("Criteria for diagnosis of Guillain-Barré syndrome," 1978) in its revised version (Asbury & Cornblath, 1990; Hadden et al., 1998; Uncini et al., 2010) with GBS, the diagnostic criteria of the European Federation of Neurological Societies/Peripheral Nerve Society Guideline on the management of chronic inflammatory demyelinating polyradiculoneuropathy- First Revision ("European Federation of Neurological Societies/Peripheral Nerve Society Guideline on management of chronic inflammatory demyelinating polyradiculoneuropathy: report of a joint task force of the European Federation of Neurological Societies and the Peripheral Nerve Society--First Revision," 2010) or earlier versions with chronic inflammatory demyelinating polyneuropathy (CIDP) and the diagnostic criteria for ALS from the World Federation of Neurology as the El Escorial Criteria (Brooks, 1994), in their revised version as the Airlie House criteria (or El Escorial revised) (Brooks et al., 2000) or Awaji criteria (de Carvalho et al., 2008), or the recently developed Gold Coast criteria (Johnsen, 2020). There are no formal criteria for progressive muscular atrophy (PMA) and primary lateral sclerosis (PLS).

Patients with subacute, severe stroke who are non-ambulatory are eligible if they can be verticalised for at least 1 hour twice a day (which is a requirement for inpatient rehabilitation at the Reha Zentrum Münster). Patients with motor neuron disease in the early, active stage of the disease will be included and patients with mild to moderate hereditary ataxia. Patients will only be included if they are able to participate in this clinical investigation over its complete duration, which will be evaluated by the study PI. Further inclusion criteria will be impairment in walking according to the neurological exam assessed by a neurologist and Functional Ambulation Categories (FAC) of 0-4, intact cognitive function as defined by a score of  $\geq 24/30$  points on the Mini Mental State Examination (MMSE) (Folstein et al., 1975).

Adult patients aged between 18 and 99 of female, male and diverse genders, of any ethnicity and German speaking verbally and written language will be included. Patients will be included if they provide a signed and dated informed consent and are willing to comply with all clinical investigation procedures.

## 5.5 Exclusion criteria

Patients will be excluded from this clinical investigation if they meet any of the criteria listed as follows.

- Concomitant disease (such as malignant disease, other severe neurological, orthopaedic or psychiatric diseases, cardiac contraindications)
- Acute, pronounced pain symptoms despite conventional pain therapy

- joint contractures, joint arthrodesis or severe spasticity (stiff/immobile joint) in the area of the lower extremity, extremely disproportionate growth of the legs and/or spinal column
- Body weight of less than 15 kg or more than 180 kg
- Body height of less than 100 cm or more than 200 cm
- Insufficient compliance e.g., patients with a serious mental illness or severe neurosis
- Significant reduction in bone density (osteopenia or osteoporosis), increased risk of bone fracture
- Osseous or joint instability (non-consolidated fractures, osteogenesis imperfecta, unstable spinal column, pseudoarthrosis, hip, knee or ankle joint instability)
- Cardiac contraindications
- Severe vascular diseases of the lower limbs
- High-grade ataxia
- Skin lesions in areas which get in contact with the device or the harness system (decubitus); infections, skin ulcers, late effects of previous injuries, especially of the lower extremity
- States of health preventing active rehabilitation (e.g., respiratory diseases, orthopaedic diseases, cognitive impairments restricting communication, aphasia, neuropsychological disorders, infections or inflammatory diseases, osteomyelitis)
- Severe apraxia
- Severe osteoarthritis in the area of the joints of the lower extremity
- Risk of autonomic dysreflexia (AD) in patients with spinal cord injury (SCI) with neurological levels of TH6 or cranial
- Reduced compliance
- Uncooperative or (self)aggressive behavior
- Cardiac diseases, e.g., heart failure and thoracotomy, uncontrolled orthostatic hypotension or other circulatory problems, circulatory disorders of the lower limbs
- Recent joint injury or endoprosthetics (e.g., total endoprosthetics, knee or hip joint replacement, reconstruction of the cruciate ligament or meniscus) with contraindicated ranges of movement or load limits
- Consolidated fractures in the area of the lower extremity within a period of 6 months after injury
- Insufficiently treated epilepsy
- Recently occurred seizures or increased risk of seizures
- Mechanical ventilation
- Lack of head control
- Long-term infusions (e.g., Baclofen pump, intrathecal pumps, PEG tube ...) or stimulators (e.g., pacemakers, nerve stimulators)
- Enterostomy/ostomy

- Sensory impairments of the lower extremities and the torso, especially reduced sensation of pain
- Pregnancy as assessed by a pregnancy test in women of childbearing age before enrolment into the study
- Any changes or adjustments to medication that has an influence on the participant's walking ability/performance will lead to the exclusion of the patient.

## 5.6 Timeline

The timeline of the clinical investigation is described as follows:

### Study-specific:

Recruitment duration: 15 months

1.2.2022 Planned start: First Patient First Visit (FPFV)

31.3.2023, 2022 Last Patient First Visit (LPFV)/Last Subject In (LSI)

30.4.2023 Planned end: Last Patient Last Visit (LPLV)/Last Subject Out (LSO)

### Patient-specific:

Active intervention duration: 4 weeks (baseline assessment, 4-week intervention, post-intervention assessment)

Figure 5 presents a flowchart of the patient-specific study process.

[figure not shown]

**Figure 5:** Flow diagram of the patient-specific study process

## 6 INVESTIGATION PREPARATION PROCEDURES

### 6.1. Investigator selection

#### Investigator selection criteria

The PI and the investigator are responsible for implementing, monitoring, and conducting all procedures related to this clinical investigation in accordance with the provisions of the clinical investigation protocol. Furthermore, the PI and investigator are responsible for making relevant decisions on the clinical investigation and medical treatment to ensure data integrity and the rights, safety, and well-being of the patients participating in the clinical investigation.

A further investigator may be included in the clinical investigation if he\*she meets the following requirements:

- appropriately qualified and experienced in the field of neurology and/or neurorehabilitation
- experience in conducting clinical investigations or appropriate training,

- availability of sufficient time for following-up on the clinical investigation,
- willingness to comply with the clinical investigation protocol,
- willingness to undergo investigation-specific training,
- Familiarity with the requirements of ISO 14155 and if otherwise, willingness to undergo appropriate training,
- Willingness to sign and comply with the clinical investigation agreement,
- Willingness to undergo auditing by sponsors or regulatory authorities.

### **Clinical Investigation Agreement**

A Research Agreement has been signed between the Reha Zentrum Münster Betriebs GmbH (RZM) and Tyromotion GmbH.

The agreement states that the purpose of this Collaboration is to systematically collect, analyse, and publish protocols and data on the clinical use of the LEXO® robotic gait trainer in the inpatient setting. A prospective comparative multiple case study will be used to investigate a variety of patients with different main diagnosis.

TYROMOTION primarily aims to collect data on effectiveness (performance) and safety (adverse events, side-effects, and drop-outs) on the LEXO® robotic gait trainer, but also on usability and feasibility, and the quality of the product.

A Purchase Order has been signed between the two parties, where Tyromotion will provide a LEXO® robotic gait trainer for the Reha Zentrum Münster that will conduct the planned clinical investigation followed by a larger randomised controlled trial.

The people involved in decision-making about this funding have no influence on the planning, conduct and publication of the clinical investigation. None of the investigators or other members of the study team receive a financial compensation for their contributions in this clinical investigation.

## **6.2. Approval of Ethics Committee**

The responsible ethics committee (EC) for this clinical investigation is the Ethics Committee of the Medical University of Innsbruck. The clinical investigation shall not begin until approval from the EC has been obtained. The EC will be informed of any subsequent changes to this clinical investigation (amendment).

## **6.3. Handling of amendments to the Clinical Investigation Plan**

To ensure a consistent study procedure in the interests of flawless data evaluation, it is not intended for there to be changes from the clinical investigation conditions planned and included in the protocol.

In exceptional cases, changes to trial conditions are possible, however. These only take place following mutual agreement between the PI, investigator and the sponsor of the study. Any change to the clinical investigation procedures set out in the protocol must be made in

writing, specifying the reasons in question, and signed by all study investigators and the sponsor. The changes will then be part of the protocol. A distinction is made between essential and non-essential amendments. Substantial amendments are subject to approval and must be submitted to the competent EC. In case of non-essential amendments (for example purely formal changes) a written notification is sufficient. In the case of significant changes that have a direct impact on the safety of study participants or other significant changes, the consent of the responsible EC and/or authorities and the patient must be obtained for protocol amendments.

The investigator has the option to stop the study overall in emergency situations between the application for a protocol amendment and such amendments being rejected or coming into effect. This is mandatory if a protocol amendment or a change in the state of knowledge for study-specific examinations occurs that leads to a potential reassessment of the risk/benefit calculation. In this case, the study will only be continued once an updated opinion has been received from the EC.

#### **6.4. Training requirements**

The clinical investigation team will undergo different trainings prior to commencement of the study. All new study team members will undergo the training outlined here.

This first and foremost includes the responsibilities of the investigator as outlined in Chapter 6.1 and ISO 14155 requirements. The PI and investigator will inform patients and obtain their informed consent

The clinical investigation team (physiotherapists) that will conduct the RAGT intervention are trained on the use of the LEXO® device by authorised personnel from Tyromotion. The training will consist of three phases: (1) provision of the training documents for the LEXO® to the study team, followed by an evaluation; (2) a two-day training consisting of a theoretical and a practical part and (3) a refresher training day a few weeks after the first training. In addition, the LEXO® is used also in the clinical routine at the Reha Zentrum Münster, which is why the physiotherapy team is familiar with the procedures.

The clinical investigation team (physiotherapists) that will perform the motor assessments in this study will undergo training from [name] who is an experienced neurological physiotherapist and senior researcher to ensure consistency.

#### **6.5. Clinical investigation materials and equipment**

Except the LEXO®, no further investigation specific materials or equipment will be provided by the sponsor.

## 6.6. Investigational device / Device accountability

The Reha Zentrum Münster will be supplied with the LEXO® well before the start of the Clinical Investigation and be installed appropriately by authorised personnel from Tyromotion. The delivery of the device will be made as outlined in a formal checklist (described below) via a semitrailer, forklift truck and lift truck and using further appropriate measures for guaranteeing a safe delivery. A suitable therapy room has been chosen for the device and checked in terms of all technical requirements, delivery details, load-bearing capacity of the ground, infrastructure, patient entry side and maintenance. A formal checklist has been completed by the technical team from Reha Zentrum Münster including a structural engineer and returned to Tyromotion. According to the Clinical Investigation Agreement, the LEXO® will remain at the study site after the end of the clinical investigation as a larger follow-up randomised controlled trial is proposed. Following both clinical investigations in a high-quality manner and publication of the study results, the purchase of the LEXO® will be complete. Details of the clinical device to allow a clear identification are described in Chapter 3.

## 7. STUDY PROCEDURES

### 7.1. Assessment and treatment schedule

The clinical investigation will comprise a screening, a baseline examination (T1), 16 intervention units over 4 weeks, and a post-intervention examination (T2).

The duration and number of the examinations (Table 1) will be used in addition to the patient's regular inpatient rehabilitation treatment. The intervention itself and some assessments will be performed as part of the clinical routine (for details, see Chapter 4). The PI, investigator and psychologists will perform any disease and cognition related examinations. All therapists conducting the movement-related assessments will be trained, and they will therefore work based on the same principles. Furthermore, the physiotherapists at the study site are using some the assessments on a daily basis (e.g., 10MWT, 6MWT), but for ensuring consistency, their training will be refreshed. The clinical investigation team (physiotherapists) that will conduct the RAGT intervention are trained on the use of the LEXO® device by authorised personnel from Tyromotion. In addition, the LEXO® is used also in the clinical routine at the Reha Zentrum Münster, which is why the physiotherapy team is familiar with the procedures. The clinical investigation team (physiotherapists) that will perform the motor assessments in this study will undergo training from [name] who is an experienced neurological physiotherapist and senior researcher to ensure consistency. In Table 8, the study procedures and schedule are presented; the table includes both the procedures which are performed ***within the clinical routine (highlighted green)*** and ***in addition to the clinical routine (highlighted yellow)***.

**Table 8:** Treatment and assessment regimen of a (screened, potential\*) study participant

| Procedure                                       | Dosage | Time                                                                            | Duration within clinical routine | Duration in addition to clinical routine |
|-------------------------------------------------|--------|---------------------------------------------------------------------------------|----------------------------------|------------------------------------------|
| Screening*                                      | 1x     | After checking for eligibility by the PI/investigator and the patient's consent | 10-15 min                        | --                                       |
| Study inclusion                                 |        |                                                                                 |                                  |                                          |
| Baseline examination (T1)                       | 1x     | Day 0-1 after study inclusion                                                   | 10 min                           | 70-90 min                                |
| Movement-related goal setting                   | 1x     | Day 0-1 after study inclusion                                                   | --                               | 5 min                                    |
| Intervention                                    | 16x    | Day 1-2 after inclusion
4x per week
(Total 4 weeks)                       | 45 min                           | --                                       |
| Semi-structured observation of the intervention | 2x     | Week 1
Week 4                                                                | --                               | No additional effort for patient         |
| Post-intervention examination (T2)              | 1x     | After 4 weeks                                                                   | 10 min                           | 70-90 min                                |

\*If the patient meets one or more exclusion criteria after screening, the patient cannot be enrolled in the study.

## 7.2. Intervention

The intervention will be a part of the routine care within inpatient rehabilitation at the Reha Zentrum Münster. The LEXO® is intended for the robot-assisted gait rehabilitation of patients with a limited ability to walk due to neurological damage to the central and peripheral nervous systems as well as due to orthopedic, geriatric and pediatric symptoms. Depending on national differences, the LEXO® is typically used in a physiotherapy environment in order to support, enhance, and intensify therapy. The repetitive movements of the lower limbs, and consequently of the gait pattern, generate intrinsic and extrinsic stimuli which favor the reorganization of the brain. Repeated, active practice and training encourages the neuronal plasticity and thus changes (adjustments) of synapses, nerve cells or even entire brain areas to recover lost movements. The LEXO® is an end-point mechatronic therapy system that allows static and dynamic body weight support, electrically driven pelvic guidance and computer-based setting of therapy parameters. The gait training addresses balance, locomotion, musculoskeletal integrity and neurocognitive control.

With regard to adaptation criteria of the RAGT, first, the different neurological disease groups will be considered, with different symptom complexes involving distinct central and peripheral nervous system (CNS, PNS) sensorimotor system areas and pathways (upper and lower motor neurons including both the cerebrum and spinal cord, extra pyramidal motor system, peripheral nervous system and cerebellum). Main motor symptoms include spasticity, rigidity, weakness, ataxia, brady- and hypokinesia and tremors and sensory symptoms include a loss in proprioception and hypesthesia among others. Second, the training will be adapted according to the individual performance level of the participants (see Table 9). RAGT will be performed within the inpatient rehabilitation routine setting for 45 minutes, 4 times a week, for 4 weeks, and will be supervised by the responsible physiotherapists. The RAGT will be integrated into patients' inpatient rehabilitation and be planned at similar daytimes to reduce patient burden and facilitate comparability. During the 45 min training period, participants will be allowed to take a break at any time, if this is desired or necessary. Based on the findings of the previous literature and with advances in walking performance, the training parameters for the different patient groups have been selected and will be progressed in difficulty (Capecci et al., 2019; Freivogel et al., 2008; Luca et al., 2013; Pohl et al., 2007; Wu et al., 2014). Explicit feedback on the walking performance will be given by the supervising therapist and implicit feedback will be provided as augmented performance feedback via a computer screen in front of the patient, based on the different measurements of parameters by the robot. For example, visual implicit feedback will be given on distance, duration, and number and length of steps.

**Table 9:** RAGT parameters and their adjustment for achieving easy to hard training levels

| Parameter                  | Easy                       | Medium                                                 | Hard                        |
|----------------------------|----------------------------|--------------------------------------------------------|-----------------------------|
| Body weight support        | ≤100% body weight support  | ≤30% body weight support                               | 0-5% body weight support    |
| Training mode and duration | ≤100% passive walking mode | ≤50% passive walking mode, ≤49% assistive walking mode | ≥50% assistive walking mode |
| Step length (27-61cm)      | 27-39 cm                   | 40-50 cm                                               | 51-61 cm                    |
| Max. training velocity     | ≤1,4 km/h                  | 1,5-2,0 km/h                                           | ≥2,0 km/h                   |

|                  |                                        |                                                                                      |                                                                               |
|------------------|----------------------------------------|--------------------------------------------------------------------------------------|-------------------------------------------------------------------------------|
| Walking distance | ≤150 steps                             | 151-500 steps                                                                        | ≥500 steps                                                                    |
| Break time       | As much as needed                      |                                                                                      |                                                                               |
|                  | Reduction of the RAGT time if required | Up to 20% of the training time (9/45 Min); either standing or reducing walking speed | 0-5% of the training time (2,25/45 Min); reducing walking speed, if necessary |

All participants will be secured with a safety harness that is able to dynamically support body weight. The harness is positioned over the LEXO® and can also be used to lift non-ambulatory participants into the training position. For participants out of Cases 1 (early, severe stroke) and severely affected participants out of Cases 7 and 8 (acute/chronic inflammatory demyelinating polyneuropathy; motor neuron disease) the initial weight support will be adjusted individually (estimated 10-40% of the total body weight) and will be reduced as rapidly as possible. The physiotherapist will assist the paretic knee control, but with further improvement participants will practice independently. If possible, participants out of Cases 2 to 8 (chronic, mild to moderate stroke; multiple sclerosis; Parkinson disease; spastic para-/tetraplegia; hereditary ataxia; acute/chronic inflammatory demyelinating polyneuropathy; motor neuron disease) will perform the RAGT without body weight support. The step length will be adjusted individually to achieve a comfortable gait velocity for all participants. The first session will start with a walking speed of 1.5 km/h, which will be increased progressively to 2.2-2.5 km/h. The intensity of the RAGT training sessions, including the amount of break-time during training, will be adapted to the individual level of impairment, presence of weakness, pain or fatigue among others.

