| Intervention               | 
Robot-assisted gait training (RAGT) using the LEXO® robotic gait trainer (Tyromotion, Graz, Austria) and supervised by the responsible physiotherapists will be performed as part of the clinical rehabilitation routine 45 minutes, 4x/week, for 4 weeks. The RAGT will be integrated into patients' inpatient rehabilitation and be planned at similar daytimes to reduce patient burden and facilitate comparability. A standard RAGT protocol will be used and adapted to the patients, with regard to the different neurological disease groups and related symptoms. Second, the training will be adapted according to the individual performance level of the participants. During the 45 min training period, participants will be allowed to take a break at any time, if this is desired or necessary. Based on the findings of the previous literature and with advances in walking performance, the training parameters for the different patient groups have been selected and will be progressed in difficulty (e.g., step length, gait speed, body weight support). Explicit feedback on the walking performance will be given by the supervising therapist and implicit feedback will be provided as augmented performance feedback via a computer screen in front of the patient, based on the different measurements of parameters by the robot. For example, visual implicit feedback will be given on distance, duration, and number and length of steps.
 |

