Secondary objective 13 of this clinical investigation is to investigate the changes in fatigue after a 4-week RAGT as assessed by the Fatigue Severity Scale (FSS).

Secondary objective 14 of this clinical investigation is to explore the amount of individual and predefined goal achievement after a 4-week RAGT as assessed by Goal Attainment Scaling (GAS).

Secondary objective 15 of this clinical investigation is to explore the changes in gait parameters (gait speed, walking distance, number of steps and step length) over the RAGT intervention period as measured by the LEXO® robotic gait trainer.

Secondary objective 16 of this clinical investigation is to explore the changes in body weight and gait support (percentage of body weight support, percentage of active/passive gait modes) over the RAGT intervention period as measured by the LEXO® robotic gait trainer.

Secondary objective 17 of this clinical investigation is to develop a theory on the causal relationships between the RAGT and study outcomes with respect to the different study patient populations. This objective does not involve patient assessments.

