## **2.4. Null-Hypothesis**

A 4-week RAGT does not change the fall rate, functional ambulation, walking speed, dynamic balance, walking distance, functional mobility, trunk movement, limits of stability with respect to trunk movements, fall-related self-efficacy, HRQoL, depression, fatigue and gait parameters in people with neurological disorders (stroke, MS, Parkinson's disease, spastic para- or tetraplegia, hereditary ataxia, acute/chronic inflammatory demyelinating polyneuropathy and motor neuron disease).

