| 1.7  | Dynamic balance                                                                                           | Four-Square Step Test (FSST)
[ambulatory patients]                                 |    | x | x  |   |
| 1.8  | Trunk movement                                                                                            | Trunk Control Test (TCT) [non-ambulatory patients]                                    |    | x | x  |   |
| 1.9  | Limits of stability with respect to trunk movements                                                       | Modified Functional Reach Test (MFRT) [non-ambulatory patients]                       |    | x | x  |   |
| 1.10 | Fall-related self-efficacy                                                                                | Falls Efficacy Scale- International Version (FES-I)                                   |    | x | x  |   |
| 1.11 | Health-related quality of life                                                                            | 5-level EQ-5D version (EQ-5D-5L)                                                      |    | x | x  |   |
| 1.12 | Depression                                                                                                | Beck Depression Inventory, second edition (BDI-II)                                    |    | x | x  |   |
| 1.13 | Fatigue                                                                                                   | Fatigue Severity Scale (FSS)                                                          |    |   | x  |   |
| 1.14 | Goal definition and evaluation of its achievement                                                         | SMART defined movement-related individual goal (a); Goal Attainment Scaling (GAS) (b) | ax |   | bx |   |
| 1.15 | Gait parameters (gait speed, walking distance, number of steps and step length)                           | Measured by LEXO® during the intervention as part of the clinical routine             |    |   |    | x |
| 1.16 | Body weight and gait support (percentage of body weight support, percentage of active/passive gait modes) | Measured by LEXO® during the intervention as part of the clinical routine             |    |   |    | x |

Abbreviation: Scr=screening; SMART=specific, measurable, attractive, realistic and terminated; c=data carryover to baseline if patient has passed the screening; BL=baseline; PI=post-intervention; IV=intervention period (at all intervention sessions)

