The first phase of the analysis will involve a descriptive analysis for all disease groups using the mean (SD) or median (range, 25th and 75th percentiles). The second phase of the analysis will include inferential statistics using a pre-post analysis of the data from the total sample (one group). For continuous data, a paired t-test will be performed and for ordinal data, a Wilcoxon Signed Rank test.

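### Endpoint 1.15 reads back LEXO speed and step length that the therapist sets under 7.2, so a rise in these values cannot be taken as an effect of the training

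*Protocol*

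**What the plan says.** **Intervention (Protocol 7.2).** "The first session will start with a walking speed of 1.5 km/h, which will be increased progressively to 2.2-2.5 km/h". Step length is adjusted by the therapist for each patient. The synopsis says that training parameters "will be progressed in difficulty (e.g., step length, gait speed, body weight support"). For Case 1 and severely affected patients in Cases 7 and 8, initial weight support "will be reduced as rapidly as possible".

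**Endpoint (2.3, and 4.8 Table 7).** Secondary objective 15 is to "explore the changes in gait parameters (gait speed, walking distance, number of steps and step length) over the RAGT intervention period". Table 7 lists item 1.15 as "Gait parameters (gait speed, walking distance, number of steps and step length") and gives its source as "Measured by LEXO® during the intervention as part of the clinical routine". It is marked for the intervention sessions only. Item 1.16 covers weight support and walking mode, from the same source.

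**Null hypothesis (2.4).** The list of things that do not change ends with "fall-related self-efficacy, HRQoL, depression, fatigue and gait parameters in people with neurological disorders". Walking speed and walking distance appear earlier in that list under their own names.

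**Analysis (8.2, Planned statistical analysis).** The second phase is "inferential statistics using a pre-post analysis of the data from the total sample (one group"), with a paired t-test for continuous data and a two-sided 0.05 level. Section 4.1 states that there is no control intervention.

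**The concern.** The quantity that the therapist sets and the quantity read as an outcome are the same. If LEXO speed is 1.5 km/h in the first session and 2.2 km/h in the last, the device record shows that the schedule was carried out. The patient's own walking may or may not have changed. Section 7.2 ties progression to advances in performance, so the settings carry some information about the patient, but nothing in the design separates that part from the schedule, and there is no comparison group.

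At stake is what may be concluded from endpoint 1.15. Section 7.8 requires a summary report to the sponsor on preliminary effectiveness, and section 4.1 intends the study to inform the hypotheses of a randomised trial. A rise in device speed could be misread in either place. The risk is greatest for non-ambulatory patients: the 10MWT and 6MWT are planned for ambulatory patients only, so for the others LEXO gives the only speed and distance data.

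**Working it through.** **1. What gait parameters means in 2.4.** Section 2.4 already lists walking speed and walking distance. The synopsis, objective 15 and Table 7 use the term gait parameters only for the LEXO data. The natural reading is that 2.4 refers to endpoint 1.15.

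**2. Prescribed change in speed (7.2).**
- Lower end: 2.2 − 1.5 = 0.7 km/h; 0.7/1.5 = 47%.
- Upper end: 2.5 − 1.5 = 1.0 km/h; 1.0/1.5 = 67%.

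**3. The other components of 1.15.**
- Step length: set by the therapist within 27–61 cm (Table 9), with no numeric progression.
- Distance = speed × time walked. At equal walking time it rises by the same 47% to 67%. Walking time is not fixed, however, because breaks are allowed at any time.
- Steps = distance / step length. Table 9 grades step count from at most 150 (Easy) to at least 500 (Hard), a ratio of at least 500/150 = 3.3. That exceeds the 1.47 to 1.67 produced by speed alone, so tolerated walking time can matter more than the speed schedule.

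**4. If the general paired t-test were applied to LEXO speed.** The protocol has no figure of its own to reproduce here: N = 4×5 + 4×2 = 28 is a sum of strata without a power calculation (5.3). With the expected 10% attrition, 28 × 0.9 = 25.2, taken as 25 completers.
- Schedule followed by all, widest possible spread (12 patients at +0.7, 13 at +1.0): mean = (8.4 + 13.0)/25 = 0.856; SD = 0.153; t = 0.856/(0.153/√25) = 28.0; p ≈ 8×10⁻²⁰.
- At a mean change of 0.7 km/h the test rejects unless the SD of change exceeds 0.7 × √25 / 2.064 = 1.70 km/h. Under full adherence the SD is at most about 0.15.

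Schedule followed in part, n = 25. These patterns are assumed, not taken from the protocol:

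| Patients who do not reach 2.2 km/h | Patients at +0.7 needed for p < 0.05 | p |
|---|---|---|
| stay at 1.5 km/h | 4 | 0.043 |
| fall by 0.1 km/h | 9 | 0.025 |
| fall by 0.5 km/h | 16 | 0.032 |

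**5. Whether the protocol orders that test.** The continuous variables listed in 8.2 are age, years of education, disease duration, 10MWT, FGA, 6MWT, TUG, FSST and MFRT. No LEXO measure is among them. Table 7 gives 1.15 neither a baseline nor a post-intervention mark. Objective 15 is worded as exploring, where objectives 1 to 13 are worded as investigating. The test can be reached only by combining 2.4 with the general rule for continuous data.

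**6. Endpoint 1.16.** Weight support and walking mode are also settings (7.2 and Table 9), but 2.4 does not mention them.

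**The case against.** The strongest reply is that the protocol plans no such test. Section 8.2 leaves LEXO data out of its variable list, Table 7 defines no pre or post value for 1.15, and section 8.1 (General aspects) gives LEXO measures a descriptive role, as a cross-check on the observed sessions. This stands. A reader might infer that following 7.2 by itself rejects the null hypothesis; the documents do not support that, because the step from 2.4 to a paired t-test on LEXO data is not written down.

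Second, the settings respond to the patient. Progression follows performance, intensity is adapted to weakness, pain and fatigue, and breaks are free. This also stands in part: distance and step count are not fixed by the schedule, and the full 27–61 cm range in Table 9 is not a change prescribed for any patient. It does not rescue gait speed, for which 7.2 gives both a start and a target.

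Third, the partial-adherence counts rest on assumed patterns. That is correct, and the answer moves from 4 to 16 patients across them.

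Fourth, the missing control group is a declared limitation, and walking speed and distance are tested off the device. Both are true. Neither says how a rise in LEXO speed should be read, and the off-device tests cover ambulatory patients only.

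A reader might also extend the point about the null hypothesis to 1.16. That fails, since weight support and walking mode are not in 2.4. It is also conjecture that LEXO speed would be singled out in the report under 7.8.

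**Conclusion.** The point holds as a minor one. For gait speed, the change read as an outcome is largely the change that 7.2 prescribes, +47% to +67%. Step length is therapist-set without a schedule; distance and step count are mixed. In an uncontrolled study a rise in these values shows training delivered and cannot be taken as an effect on the patient.

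False rejection of the gait-parameter part of the null is near certain only if two conditions are met: the general paired t-test is applied to LEXO speed, and most patients follow the schedule. If the data are only described, what remains is a problem of interpretation, created by naming gait parameters in 2.4. Endpoint 1.16 shares the interpretive problem only.

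The conclusion assumes that the increase in 7.2 runs over the four weeks. The sentence could also mean an increase within the first session, but progression across sessions is the more natural reading. The primary feasibility endpoint, the 10MWT and the 6MWT are untouched.

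**What to change.** - **2.4:** delete gait parameters, so that the list ends with depression and fatigue.
- **2.3, 4.8 and the matching synopsis text:** describe 1.15 and 1.16 as training delivered (device settings and output), reported descriptively per session and by Case, with no pre-post test and no effectiveness claim. Keep effect statements on walking speed and distance to the 10MWT and 6MWT in ambulatory patients.
- **7.2, a separate small repair:** write that 1.5 km/h is the default starting speed, lower as tolerated. As it stands, every first session starts at 1.5 km/h, while Table 9 caps the Easy level at 1.4 km/h.

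The cost is a few words in 2.4, a label in 2.3, 4.8 and the synopsis, and one clause in 7.2. The same LEXO data are collected, with no new assessment and no added patient burden. Reported this way, they also show what the sessions counted under the 75% adherence criterion contained.
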